## Abstract

**Background:**

Clinical studies are being conducted in less strict conditions in order to establish an adequate scientific basis for decision making. The aim of this pragmatic randomized clinical trial is to evaluate the effectiveness of single and multiple-surfaces restorations performed following the Atraumatic Restorative Treatment (ART) premises compared with Conventional Treatment (CT) using bulk fill composite restorations in primary and permanent teeth.

**Methods/design:**

A total of 1,214 5-to-13 year-old children with at least one single or multiple-surface dentin caries lesion in primary or permanent molars will be selected in public schools of Barueri-SP, Brazil. The participants will be randomly assigned into 2 groups: CT (caries removal with bur and restoration performed with Scotchbond™ Universal Adhesive system associated with Filtek Bulk Fill – 3 M/ESPE) and ART (Caries removal with hand instruments and restoration with high viscosity glass ionomer cement Ketac Molar Easy Mix – 3 M/ESPE). Ten untrained dentists will perform the treatment in in dental offices located at public schools. The restorations will be evaluated after 6, 12 and 24 months by an independent trained and calibrated examiner. The restoration and tooth survival, the cost-effectiveness analysis between the two groups and the operators’ preferences regarding the techniques will be also evaluated. Kaplan-Meier survival analysis and log-rank test will be applied for the restoration and tooth survival. All the average event rates in the two groups will be modelled and compared with a Cox proportional hazard shared frailty model since there is an operator-cluster effect. The significance level for all analyses will be 5 %.

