### Study design

The design of this project comprises different dentitions (primary and permanent teeth) and different surfaces (single or multiple-surface).

This is a pragmatic, two-arm, parallel group, patient-randomized trial which has 10 dentists as operators in dental offices located at public schools. The schedule of enrolment, interventions, and assessments diagram is showed in Fig. 1.

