### Sample description

Since single and multiple-surfaces cavities are going to be restored, both in primary and permanent teeth, and the difference expected between those groups are not the same, four sample size calculations were done.

The sample size calculation was performed using the website statstodo.com based on the primary outcome - treatment survival, using log-rank test in survival analysis. For the single surface, the calculation was based in an absolute difference between the survival rates of CT vs. ART of 15 % while for the multiple-surfaces, the absolute difference considered was 20 %. This involved a two-tailed test based on survival rate reported for ART [10] after 2 years of follow- up, α of 5 and power (strength) of 80 %. The sample size was increased 20 to compensate for possible losses during the study and 40 % to compensate operators-cluster effect. This gave a final sample size of 1214 teeth (described in Table 1).

**Table 1 Tab1:** Sample size calculation description

Tooth type	Surface	Survival Rate reported for ART (2 years)	Sample size	+20 % possible losses	+40 % operator-cluster effect
Permanent	Single surface	93	181	253	304
	Multiple surfaces	62	165	231	278
Primary	Single surface	93	181	253	304
	Multiple surfaces	41	195	273	328
				Total	1, 214

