### Randomization

The randomization lists were computer generated (www.randomization.com), based on randomly permuted blocks of varying size (2, 4 or 6, randomly sampled with equal probability) and stratified for operator (1–10), dentition (primary/permanent) and surface (single/multiple). Opaque, sealed and sequentially numbered envelopes will be used to randomize the participants into the treatment groups (ART and CT).

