
### Data analysis

Data will be analyzed according to the protocol principle. First, to compare treatments’ and teeth longevity, both Kaplan-Meier survival analysis and Log-rank test will be applied. The association between restoration longevity and caries experience or type of cavity will be evaluated using Cox Regression.

As we have a cluster-effect related to the numbers of operators of this trial and its contextual variables (such as age, work experience and technique preference), the average event rates in the two groups over the two year study period will be then modelled and compared with a “shared frailty” model. This model is an extension of the Cox proportional hazard model that includes a frailty term (a statistical expression for random effect, unrelated to the clinical concept of frailty) to take dependency of events within a contextual (correlation between different falls by the same operator) into account. All participants will be included in the model until their last time point, which means that the model will use all available data right up to the time of withdrawal or trial completion. For each outcome, we will present the hazard ratios and 95 % confidence intervals for the intervention, adjusted by operator.

The variance analysis will be used to compare groups in relation to the cost after determining data normality through the Kolmogorov-Smirnov test. Poisson analysis will be used to assess the association between the treatment group, the preference of professionals and the cost of treatments. The significance level will be set in 5 %.

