**Fig. 2 Fig2:**
[figure not shown]
PRECIS domains diagram

As a pragmatic study, the conditions reported in this protocol are similar to those in real dental practice and the operators are dentists who work for the public health system. The decision to not perform any training for the operators is to maintain a closer representation of the dentists’ reality in dental practice, since they have different backgrounds of undergraduate learning. In that way, the operators only will receive one guideline on how to prepare, restore and finalize the restoration according to the original procedures of ART [2]. Regarding the procedures performed in the CT group, as all the dentists are used to do composite resin in their daily clinical practice, they will receive only some information about the manufacturer specifications for using these new materials. Due the evident differences between the techniques and materials used in each group presented in this trial, it is not possible to blind the patients, operators or evaluators.

Few clinical studies are reported in the literature using a bulk fill composite resin [9, 20] and to the best of our knowledge this is the first study to use this material also for restoring primary teeth. As this material can be used in a single increment until 4 mm allied to the use of a universal adhesive, which allows the self-etch technique, the clinical time may be shortened, reducing the contamination probability. As no rubber dam is available in public health dental practice in Brazil, the use of these materials could be an answer to improve the conventional treatment longevity.

In cases where the child has more than one eligible cavity in the same dentition and surface (for example: two single-surface cavities in a primary molar in the same child), only one cavity will be randomly selected. In case of different teeth (permanent and primary) or different surfaces (single or multiple-surface), more than one tooth can be selected for the research, since the analysis of each group will be done separately (for example: one single-surface in a primary molar and one single surface in a permanent molar in the same child). In this case, each tooth will be randomly allocated to the intervention group since the analyses are going to be done separately according to dentition and surface.

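### The protocol gives two units for sample size and randomisation, child and tooth, and does not say whether its models are fitted per stratum or allow for several teeth from one child

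*Protocol article*

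**What the plan says.** **Unit of sample size.** The abstract (Methods/design) counts "A total of 1,214 5-to-13 year-old children with at least one single or multiple-surface dentin caries lesion". Sample description, after four separate calculations, concludes: "This gave a final sample size of 1214 teeth".

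**Unit of randomisation.** Study design calls this a "two-arm, parallel group, patient-randomized trial". The abstract and the Randomization section also assign participants, although the lists are stratified by operator and by two features of the tooth: dentition and surface. The Discussion (text after Fig. 2) says that a child with several eligible cavities of the same dentition and surface type contributes one of them, chosen at random. A child with eligible cavities in different strata may contribute more than one tooth, and "each tooth will be randomly allocated to the intervention group since the analyses are going to be done separately" by dentition and surface.

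**Analysis.** Data analysis does not repeat that the strata are analysed separately. It states: "The association between restoration longevity and caries experience or type of cavity will be evaluated using Cox Regression". It adds a shared frailty model comparing the two groups with operator as the cluster, and cost models. None of these names a stratum, and none has a term for the child.

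**The concern.** The two descriptions are different trials. In a patient-randomised parallel-group trial each child has one treatment and 1,214 is a recruitment target for children. In a tooth-randomised trial a child can have ART in one tooth and composite in another, and the number of children is unknown until recruitment ends. A reader cannot tell when recruitment is complete or what the trial report should call the randomised unit.

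The unit also governs the analysis. Several teeth per child are harmless only if every model is fitted within one stratum. If a model pools strata, teeth from the same child are correlated, and whether ignoring this matters depends on which factor is being tested and on which unit was randomised.

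**Working it through.** **1. What 1,214 counts.** Inputs from Sample description and Table 1: two-sided 5%, 80% power, log-rank test, ART survival of 93%, 62% and 41%, differences of 15 points (single surface) and 20 points (multiple surfaces). The direction of each difference is not stated; the directions below are those that reproduce the table. A 1:1 ratio is assumed, as the block sizes are even.

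Freedman's formula, with HR = ln(q)/ln(p): events E = (1.960 + 0.842)² × ((1 + HR)/(1 − HR))², and N = E / mean event proportion, both arms together.

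| Survival p vs q | HR | E | Mean event proportion | N | Table 1 |
|---|---|---|---|---|---|
| 93% vs 78% | 3.424 | 26.15 | 0.145 | 180.3 → 181 | 181 |
| 62% vs 82% | 0.415 | 45.95 | 0.280 | 164.1 → 165 | 165 |
| 41% vs 61% | 0.554 | 95.51 | 0.490 | 194.9 → 195 | 195 |

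Multiplying by 1.4 and then 1.2 gives 304, 278, 304 and 328, and 304 + 278 + 304 + 328 = 1,214. (The intermediate column is the ×1.4 step although it is headed +20%; the two headings look swapped, with no effect on the total.) Each stratum count is a number of restored teeth, so the sum is a number of teeth. It equals a number of children only if no child enters two strata.

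**2. How many children.** Two dentitions × two surface types gives at most four teeth per child, one per stratum. The most is 1,214 children, with one tooth each. The fewest is the size of the largest stratum, 328, since each of its teeth needs a different child (1,214/328 = 3.7 teeth per child). Conversely, 1,214 children yield more than 1,214 teeth as soon as one child contributes two.

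**3. Mixed treatment within a child.** With independent 1:1 allocation of each tooth, a child with k teeth receives both treatments with probability 1 − 2 × (1/2)^k: 50% for two teeth, 75% for three, 87.5% for four. That is not a patient-randomised parallel design.

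**4. Within one stratum.** Each child gives one tooth, so there is no within-child clustering in any of the four separate comparisons.

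**5. If strata are pooled with no child term: child-level factor.** Design effect DEFF = 1 + (m − 1) × ICC. True/naive SE = √DEFF. Actual error of a nominal 5% test = 2 × (1 − Φ(1.96/√DEFF)). Teeth per child m and the ICC are assumptions; the protocol gives neither.

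| m | ICC | DEFF | True/naive SE | Naive SE too small by | Error |
|---|---|---|---|---|---|
| 1.5 | 0.2 | 1.10 | 1.05 | 5% | 6.2% |
| 2 | 0.2 | 1.20 | 1.10 | 9% | 7.4% |
| 2 | 0.5 | 1.50 | 1.22 | 18% | 11.0% |

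**6. If strata are pooled with no child term: other factors.** A simulation used a pooled linear model for 24-month failure (not a Cox model), a child effect on the log hazard with SD 0.5 to 1.0, two or four teeth per child, 1,214 teeth (1,212 at four per child) and 8,000 runs per setting; these settings are assumptions.

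| Effect | True/naive SE | Type I error |
|---|---|---|
| Treatment, each tooth randomised | 0.99 to 1.01 | 5.0 to 5.2% |
| Treatment, child randomised | 1.03 to 1.30 | 5.4 to 13.1% |
| Child-level covariate | 1.04 to 1.31 | 5.7 to 13.7% |
| Surface type | 0.88 to 0.99 | not computed; naive SE too large |

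**The case against.** The strongest reply concerns the analysis, not the unit. The Discussion says that analyses are separate by dentition and surface, and Data analysis never declares a pooled model. Cavity type is not defined there: it could mean a feature that varies within a stratum, such as cavity size or contact, both of which the eligibility section says will be recorded and analysed. Caries experience belongs to the child, but a Cox model on it within one stratum has one tooth per child and no clustering. A condensed article may leave such detail to a fuller plan.

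This stands in part. Pooling is implied, not stated, so the modelling point must be conditional. It does not remove the need for clarity: if cavity type means single versus multiple surface, that model has to pool, and the frailty model compares two groups with no stratum named.

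A reader might also infer that every standard error in a pooled model would be too small. The checks do not support that. With teeth randomised independently the treatment standard error is about right, and for surface type it is too large. It is too small for child-level factors, and for treatment only if the child is the randomised unit.

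None of this answers the contradiction between children and teeth, or between patient and tooth allocation.

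**Conclusion.** The contradiction is certain and rests only on the text and on Table 1. The figure of 1,214 is a number of teeth, and the abstract's count of children does not follow from the calculation. The number of children lies between 328 and 1,214, and the patient-randomised label does not fit allocation of each tooth.

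The modelling consequence is conditional on strata being pooled without a child term. In that case, with an assumed 1.5-2 teeth per child and ICC of 0.2-0.5, naive standard errors for caries experience are about 5-18% too small and a nominal 5% test errs about 6-11% of the time. The wider simulation settings, which go up to four teeth per child, reach 13.7%.

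One might conclude that the primary treatment comparison is compromised. It is not: within each stratum every child counts once. This is an inconsistency that should be corrected, and it does not invalidate the main comparison.

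**What to change.** - State one unit of sample size and one unit of randomisation, the same in the abstract, Study design, Sample description, Randomization and Discussion. Table 1 and the allocation text in the Discussion imply teeth, at most one per dentition-surface stratum per child, each allocated separately. If children are in fact the randomised unit, the Discussion must change instead.
- Report the number of children and the number of teeth separately, with the number of children who contribute more than one tooth and who receive both treatments.
- In Data analysis, state for each model (Cox on caries experience and cavity type, frailty, cost) whether it is fitted per stratum. Define cavity type. Where strata are pooled, add child-clustered robust variance or a child frailty alongside the operator term.
- Keep the four separate stratum analyses as the treatment comparison.

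The cost is wording plus one option in any pooled model. It needs the child's code on every tooth record. The protocol says that participants are coded by number, so the link should be available, but it does not say that tooth records carry the code, and this should be checked.

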**Discussion:**

Our hypothesis is that despite similar expected effectiveness between ART using high viscosity GIC and conventional treatment using bulk fill composite resin when treating single or multiple-surface in posterior primary and permanent teeth, ART will present superior cost-effectiveness. The results of this trial will support decision-making by clinicians and policy makers.

**Trial registration:**

NCT02568917. Registered on May 10th 2015.

**Electronic supplementary material:**

The online version of this article (doi:10.1186/s12903-016-0260-6) contains supplementary material, which is available to authorized users.

## Background

Currently, both in medicine and dentistry, clinical studies are being conducted in less strict conditions, closer to those found in practice in order to establish an adequate scientific basis for decision making, the so-called pragmatic clinical trials. Trough those studies design, a closer representation of the characteristics of the patient and how the intervention will take place in real clinical practice is expected [1]. However, few pragmatic studies were conducted in dentistry, especially when the primary outcome is the effectiveness of restorative treatment [2, 3].

The Atraumatic Restorative Treatment (ART) has been considered an innovative, painless and minimally invasive treatment for the management of caries [4, 5]. Initially, this treatment was recommended to populations in which the technical and operational conditions were unfavourable [6]. However, ART has been proven to be a high quality and reliable approach in the management of dental caries, and became, therefore, suitable for all patients, regardless of the economic and social situation [7, 8]. Allied to these indications, the fact anesthesia, rubber dam and rotary instruments are not required, stimulated the ART use in the public and private health systems compared to conventional treatment (CT).

In order to reduce the clinical time of the conventional restorative procedure, a new concept in composite resins is emerging [9]. The “bulk fill” composite which intended to reduce the polymerization shrinkage stress (main drawback of composite resin), has been gaining strength in the dental market. Thanks to its technical ease of use, since the restorations can be performed by a single increment of resin (up to 4 mm), this material can be an alternative to restorations in public health, in which rarely rubber dam is employed. As the material is inserted in one increment, the time expended to perform the treatment can be shortened, thus reducing the chance of contamination and possibly increasing restoration longevity.

When it comes to the real applicability of ART compared to CT using composite resin, there is little evidence regarding both the longevity of these restorations and the preference of dentists on the use of each technique [2, 3].

Due to the need of establishing the best scientific evidence about restorative treatment, the aim of this pragmatic clinical trial is to evaluate the effectiveness of single and multiple-surface ART-restorations performed compared to the CT in primary and permanent molars.

## Methods/Design

The present protocol follows the guidelines of the Standard Protocol Items: Recommendations for Interventional Trials (SPIRIT) (Additional file 1).

### Ethical aspects and registration

This clinical trial was approved by the Local Ethics Committee of Research in Humans (#1.293.897) and registered in the database for registration of clinical studies Clinicaltrials.gov (registration no. NCT02568917).

The study will be conducted in Barueri, a city in the state of São Paulo, Brazil. Informed consent will be obtained from children’s parents or guardians before participation in the study and each child must also assent to participate.

All participants will be encoded by a number in order to guarantee information confidentiality. In case of files containing identifiable data, those will be stored in locked filing cabinets and final dataset will be available for inspection under coordinator’s endorsement. Thus, there is no Data Monitoring Committee. Only researchers will have access to participants’ information. Independent surveillance of trial data collection, management and analysis is undertaken by the main investigator ([name]) who has overall responsibility for the study and is in charge of the data. The collected data will be subject to audition by the coordinator; by raising data queries if necessary. This protocol has been peer-reviewed by the funding agency.

The adverse events related to the CT or ART (groups investigated in this trial) are those related to dental treatment. These effects are similar to those found during a conventional treatment performed in the pediatric dentistry clinical practice. The operators of this project will conduct all dental treatment needs of the children participating in this trial.

### Study design

The design of this project comprises different dentitions (primary and permanent teeth) and different surfaces (single or multiple-surface).

This is a pragmatic, two-arm, parallel group, patient-randomized trial which has 10 dentists as operators in dental offices located at public schools. The schedule of enrolment, interventions, and assessments diagram is showed in Fig. 1.

**Fig. 1 Fig1:**
[figure not shown]
Clinical trials flowchart

### Sample description

Since single and multiple-surfaces cavities are going to be restored, both in primary and permanent teeth, and the difference expected between those groups are not the same, four sample size calculations were done.

The sample size calculation was performed using the website statstodo.com based on the primary outcome - treatment survival, using log-rank test in survival analysis. For the single surface, the calculation was based in an absolute difference between the survival rates of CT vs. ART of 15 % while for the multiple-surfaces, the absolute difference considered was 20 %. This involved a two-tailed test based on survival rate reported for ART [10] after 2 years of follow- up, α of 5 and power (strength) of 80 %. The sample size was increased 20 to compensate for possible losses during the study and 40 % to compensate operators-cluster effect. This gave a final sample size of 1214 teeth (described in Table 1).

**Table 1 Tab1:** Sample size calculation description

Tooth type	Surface	Survival Rate reported for ART (2 years)	Sample size	+20 % possible losses	+40 % operator-cluster effect
Permanent	Single surface	93	181	253	304
	Multiple surfaces	62	165	231	278
Primary	Single surface	93	181	253	304
	Multiple surfaces	41	195	273	328
				Total	1, 214

### PRECIS (Pragmatic-Explanatory Continuum Indicator Summary) domains

#### Elegibility/Recruitment/Setting

The participants of the trial are those who would receive dental treatment in a usual care. No extra effort will be made to recruit more participants. All children that have at least one single or multiple-surface caries lesion in a primary or permanent posterior tooth and who seek for treatment in one of the participating centers are eligible for this trial.

Only the children whose parents or legal guardians signed the informed consent and who assent to be part of the study will be included in the research. All phases of this trial will be carried out in the dental clinic located at public schools. As radiographic facilities are not available in this setting, only clinical diagnosis will be used.

As this trial aims to evaluate the restoration and tooth survival, the tooth of interest should not present any associated fistula, abscess, pulp exposure, historical of spontaneous dental pain or mobility.

Even when children do not present a cooperative behavior, they will be included in this trial, as it is a common problem in pediatric dentistry clinical practice. Other variables like size of the cavity, approximal or occlusal contact and caries experience will also not be considered as exclusion criteria. All data will be recorded and further analysed to manage if there is any influence of those clinical factors on the survival rate of the restorations.

Recruitment will take place from March to November 2016. Each participant will be enrolled in the study for about 25 months: 1 month for RCT diagnosis and treatment, followed by a 24-month observational period. Details are illustrated in Fig. 1.

